#### Description of the mobile app

The mobile app has four sections: the first one is called “patient” (Picture 1) and comprises two parts: progression and medical record. In the first part, users can upload data regarding their heart rate, respiratory rate, arterial oxygen saturation, capillary refill, dyspnea level, fraction of inspired oxygen, and any relevant observations (additional results). In the second part, patients can see their vital sign trends within the last week, which has been included to simplify the decision-making process regarding the requirement for oxygen therapy. In this sense, it is worth mentioning that AppO_2_ displays a visual alarm if the vital signs uploaded fall outside predetermined limits. Moreover, patients’ data can be deleted once the follow-up period is terminated.

The second section is called “vital signs” (Picture 2) and explains in detail the way in which each vital sign is measured to ensure the highest level of accuracy of input data. Moreover, there is a third section called “formulas” (Picture 3), in which the duration of an oxygen cylinder and the oxygen saturation/fraction of inspired oxygen ratio can be estimated.

### Formulas: duration of an oxygen cylinder.

where P is pressure of the cylinder; RP is residual pressure; F is conversion factor of the cylinder; and Fl is oxygen flow intended to be used.

### SO_2_/FIO_2_ ratio

For a noninvasive saturation monitoring of the patient, the SaO_2_/FiO_2_ (oxygen saturation/fraction of inspired oxygen) formula will be used [32–34]. In this manner, gasometric assays are avoided, and continuous respiratory monitoring can be achieved. Oxygen saturation levels will be recorded, in addition to the fraction of inspired oxygen (FiO_2_) that is determined on the basis of the oxygen system required by the patient. This value will be recorded on a weekly basis. Note that SO_2_ is arterial oxygen saturation and FiO_2_ is the fraction of inspired oxygen.

The fourth section is called “About”. In this section, patients and caregivers will have access to useful information regarding the management of oxygen at home such as relevant safety and hygiene advice regarding oxygen supplies and systems. Moreover, it will have a Frequently Asked Questions section (FAQs) about the management of oxygen at home, which will include the following questions:Why do I have to use oxygen at home?How do I use my oxygen systems?When do I have to use my oxygen systems?Will I use oxygen forever?Can I increase oxygen liters based on my prescription?How can I clean my oxygen supplies and system?When can I remove my oxygen supplies?Is my health negatively affected by oxygen? (Table 1)

**Table 1 Tab1:** Items from the World Health Organization Trial Registration Data Set

Data category	Information
Primary registry and trial identifying number	ClinicalTrials.gov NCT04820790
Date of registration in primary registry	March 29, 2021
Secondary identifying numbers	Not Applicable
Source(s) of monetary or material support	Todomed
Primary sponsor	Todomed
Secondary sponsor(s)	Not applicable
Contact for public queries	[name], magister, + [contact]
Contact for scientific queries	TodoMed, Colombia
Public title	Mobile Application for Monitoring Patients with Home Oxygen. A Protocol of a Randomized and Controlled Clinical Trial
Scientific title	Mobile Application for Monitoring Patients with Home Oxygen. A Protocol of a Randomized and Controlled Clinical Trial
Countries of recruitment	Colombia
Health condition(s) or problem(s) studied	Oxygen-therapy
Intervention(s)	Experimental: Experimental Group 1 The efficiency of the mobile app in the follow-up of patients with home oxygen will be evaluated during 6 months No Intervention: Intervention Group 2: Regular monitoring of the home oxygen without mobile app during 6 months
Key inclusion and exclusion criteria	Inclusion Criteria: Individuals of 18 years of age and older Patient with PaO2 < 60 mmHg, SO2 < 89% and dyspnea. Patients with home oxygen therapy enrolled in-home care programs during the study period. Time of evolution of the disease greater to one year Patients who express their willingness to participate in the study through their informed consent. Exclusion Criteria: Patients with the following exceptional situations will be excluded from the study: Patients with invasive and/or non-invasive mechanical ventilation Patients with the inability to operate a mobile application or those who do not have a smartphone with an operating system (Android or iOS) and available data connection.
Study type	Interventional (Clinical Trial), Allocation: Randomized Intervention Model: Parallel Assignment Masking: Single (Participant) Primary Purpose: Supportive Care
Date of first enrolment	June 1, 2021
Target sample size	44
Recruitment status	Not yet recruiting
Primary outcome(s)	Recognition of self-management of dyspnea and through the mobile app (Time Frame: up to 12 weeks for 6 months)
Key secondary outcomes	Saint George questionnaire for the assessment of health-related quality of life (Time Frame: up to 6 weeks for 6 months)

Criteria for discontinuing or modifying allocated interventions for a given trial participant

Voluntary abandonment, death.

Participant Retention

Once a patient is enrolled or randomized, the study site will use reasonable efforts to follow the patient throughout the study period.

Interaction between users and the AppO_2_ mobile app.

The app has a user-friendly design through which patients can intuitively access the different sections and accordingly register their data. When patients log in for the first time, they have to enter their basic data such as full name, healthcare system affiliation regime, birth date, sex, and diagnosis. Once a patient’s account has been created, the following healthcare-derived clinical results can be recorded in the “progression” section: heart and respiratory rates, SO_2_ measured with a pulse oximeter, level of dyspnea, capillary refill, and fraction of inspired oxygen. After recording a second progression, patients can see a line graph showing trends for each vital sign. Regarding the formulas included, users just have to select the fields of those elements whose values are not predetermined. This ensures that the use of formulas is not limited by a lack of information regarding certain values. In cases with limited and standardized available options (e.g., type of cylinder), there is a drop-down list such as that the desired option can be quickly selected.

### Reports

The mobile app will have a section called “changes”, which will comprise notifications made to users when they register changes in the management and frequency of home oxygen therapy such as reports of changes of systems and oxygen flow. If patients do not upload their management behavior report, the app will send a notification to encourage such upload. Hernández de los Reyes et al. [35] evidenced that the best time to send such remainders can be selected based on a) the best time of the day to receive notifications as determined by users of the app and b) the possibility of sending messages at time points in which users’ routine or sleeping times are not interrupted. For these reasons, we have determined that the best adherence will be achieved at time points in which patients have no commitments (one notification in the morning and one at night, twice a month during the 6 months of the intervention).

### Ethical considerations

Ethical approval and informed consent. The ethical consent approved by the participants will be obtained in writing.

This study protocol complies with the Declaration of Helsinki for medical studies and has been approved by the Ethics and Bioethics Committee of Universidad Santiago de Cali, and has been registered on the Clinicaltrials.gov platform (Identifier: NCT04820790). All patients will receive written communication of the purposes of the study and will sign an informed consent pursuant to current regulations. Patients shall sign the informed consent accepting the study conditions.

• Consent for publication: institutional consent form. Has been submitted through the platform.

• Availability of data and material: not Applicable. As the submitted article is a clinical trial protocol, the authors do not have a database to share in any public repository. Once the clinical trial is completed, the investigators will decide the most appropriate way to make them public.

#### Statistical analysis

A descriptive analysis of the study variables will be performed, characterizing patients, generating graphs and frequency tables for qualitative variables, and estimating measures of central tendency (mean), dispersion (standard deviation) and position (distribution limits and range) for quantitative variables.

For bivariate analysis, a Student’s t test will be conducted to compare two means, whereas a chi-squared test and Fisher’s exact test will be used for qualitative variables. For analyzing three mean values or more, a repeated measures analysis of variance (ANOVA) will be used. Multiple lineal regression models will be applied to adjust the impact of the use of the app and to remove the effect of confusing factors, estimating standardized beta coefficients, an adjusted determination coefficient, and residual values. An alpha error of < 5% will be accepted and 95% confidence intervals (95% CI) will be estimated for all statistical analysis, and the SPSS Statistics software, 25.0 version (IBM Corp) will be used.

**Formal committee**: no need for a formal committee as the trial is short with minimal known risks.

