### Sample size estimation

A total of 32 subjects (16 for the experimental group and 16 for the control group) should be recruited to obtain a 1:1 ratio, 80% power (beta error = 20%) and 95% safety (alpha error = 5%), and assuming according to the results evidenced by Nguyen et al. [28] that intervention in the experimental group will cause a 3% increase, with ± 6 standard deviation, in the identification of dyspnea self-management. A final sample size of 44 subjects (22 for the experimental group and 22 for the control group) has been determined to minimize the effects of potential losses in statistical power.

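### The planned repeated measures ANOVA keeps only patients with complete series, and neither the t test nor the planned regression names the baseline outcome

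*Protocol article*

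**What the plan says.** The Statistical analysis section of the protocol article fixes two methods for means. For two groups, a Student's "t test will be conducted to compare two means". For longer series, "For analyzing three mean values or more, a repeated measures analysis of variance (ANOVA) will be used". The same paragraph adds multiple linear regression to adjust the app effect for confounding, with SPSS 25 as the software. It does not name the baseline value of the outcome as a covariate, and the list of independent variables that follows the outcomes does not include it.

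The Outcome variables section follows each outcome from randomisation to first progression or death, to a maximum of six months. The criteria for discontinuation, given after Table 1, are voluntary withdrawal and death.

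Under Sample size estimation the target is "A total of 32 subjects (16 for the experimental group and 16 for the control group) should be recruited to obtain a 1:1 ratio", on the assumption that "intervention in the experimental group will cause a 3% increase, with ± 6 standard deviation, in the identification of dyspnea self-management". The total is then raised to 44, a number that "has been determined to minimize the effects of potential losses in statistical power". No loss rate is stated.

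**The concern.** Two features of the named methods fit this design poorly.

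- **Complete cases.** Repeated measures ANOVA in the standard SPSS general linear model procedure deletes a patient who lacks any one time point, together with all that patient's other measurements. Here assessment ends at progression or death, so some series will be short by design, and short for reasons linked to the patient's condition. The deletion costs precision and may bias the comparison.
- **Unused baseline.** A two-sample t test on a follow-up score ignores the baseline score. In a trial this small, a covariate that predicts the outcome is a source of precision that needs no further patients. The planned regression could use it but does not say that it will.

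**Working it through.** **Inputs from the protocol article.** Difference 3, SD 6, alpha 5%, power 80%, 16 per arm before and 22 per arm after the allowance for losses (Sample size estimation). Sidedness is not stated; two-sided is taken.

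**Assumed, because the article does not give them.** Correlation r between baseline and follow-up of 0.3, 0.5 or 0.7; a continuous score measured at baseline in both arms; SD 6 as the SD of raw scores.

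**1. The plan's own figure.** Two-arm formula: n per arm = 2 × (1.96 + 0.84)² × 6² / 3² = 62.8, so 63 per arm (50 if one-sided). The plan has 16. The one-group or paired formula, (1.96 + 0.84)² × 6² / 3² = 31.4, gives 32, which matches the stated total but is not a two-arm comparison. Power below is therefore low whatever analysis is chosen.

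**2. Implied loss.** (44 − 32) / 44 = 12/44 = 27.3%, that is 6 of 22 per arm.

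**3. Power of the t test (noncentral t).** Noncentrality = 3 / (6 × √(2/n)).
- n = 16: 1.41 on 30 df, power 28%.
- n = 22: 1.66 on 42 df, power 37%.

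**4. Baseline adjustment (ANCOVA).** The SD becomes 6 × √(1 − r²), with one df fewer.

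| r | residual SD | power, 16 per arm | gain over t test (28%) | power, 22 per arm | n per arm for 80% |
|---|---|---|---|---|---|
| 0.3 | 5.72 | 30% | 2 points | 40% | 58 |
| 0.5 | 5.20 | 35% | 7 points | 46% | 48 |
| 0.7 | 4.28 | 48% | 20 points | 62% | 33 |

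**5. Simulation with losses.** 4000 runs per setting; baseline plus two follow-ups with equal correlation r; effect 3 at both follow-ups; 6 of 22 per arm missing the last visit completely at random. The ANOVA test is the group-by-time term with baseline as one level. The all-data model is a likelihood estimate of the last-visit difference adjusted for baseline.

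| r | completer t test | completer ANOVA | completer ANCOVA | baseline-adjusted, all data |
|---|---|---|---|---|
| 0.3 | 28.5% | 21.3% | 29.8% | 29.2% |
| 0.5 | 27.9% | 28.1% | 34.4% | 34.4% |
| 0.7 | 28.2% | 44.5% | 47.5% | 48.2% |

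- All-data model minus completer ANOVA: 7.9, 6.3 and 3.7 points.
- All-data model minus completer ANCOVA: −0.6, 0.0 and +0.7 points. The simulation error is about √(0.3 × 0.7 / 4000) = 0.7 points, so these are indistinguishable from zero.

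**6. The same simulation with nobody missing.** ANOVA 28.8%, 37.5%, 57.2%; baseline-adjusted model 39.3%, 44.2%, 59.3%; gap 10.5, 6.7 and 2.1 points. The advantage over ANOVA is there without any loss, so it is not a measure of what deletion costs.

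**The case against.** The strongest reply is that the article also plans an adjusted regression, that a condensed article may leave the covariate list and the handling of missing values to an analysis plan that is not shown, and that the gain rests on a correlation nobody has stated. Much of this stands. The absence of a missing-data method is no finding. What remains is an objection to methods the article does name: an ANOVA that conventionally needs complete series, and a t test without baseline.

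Several stronger readings are tempting and are not supported:

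- *That the plan has no adjusted analysis.* It has one; the gap is that the baseline outcome is not named in it.
- *That the t test also drops anyone with a missed visit.* It drops only patients who lack the value being compared.
- *That ANOVA necessarily wastes baseline.* If baseline is one of its time points, the group-by-time term uses it. The group main effect would be diluted in that layout, but the article does not say that this is the term to be tested.
- *That the trial plans for 27% loss.* This is inferred from 32 and 44.
- *That power would rise from 37% to 46–62%.* Those figures need all 22 per arm analysed and r of 0.5 to 0.7. With the implied losses and r as low as 0.3, the gain over the t test is 2 points.
- *That keeping incomplete patients is what restores power.* Under random loss of the last visit it adds almost nothing beyond baseline adjustment.

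The simulation took losses to be completely random, so it says nothing about the size of any bias.

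**Conclusion.** The concern holds in limited form. The ANOVA as named conventionally discards incomplete series in a trial whose follow-up rules produce them, and no planned analysis names the baseline outcome. With 16 completers per arm, baseline adjustment takes power from 28% to about 30%, 35% or 48% at r = 0.3, 0.5 or 0.7, and a baseline-adjusted all-data model beats completer ANOVA by about 4 to 8 points.

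These sizes rest on the assumed r, a two-sided test, and a continuous score with a baseline in both arms. The last condition is clear for the Saint George and Borg scores. It is not established for the primary outcome, which is identified through an app that controls do not use.

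The change is worth making because it is nearly free, but it does not rescue the trial. Even with it, power under the implied losses stays at about 29–48%, because the stated inputs call for 63 per arm. That shortfall is a separate and larger problem.

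**What to change.** For continuous outcomes measured at baseline in both arms (Saint George, Borg, and the primary outcome if it is such a score):

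- **Repeated measurements.** Replace repeated measures ANOVA with a linear mixed model (SPSS MIXED) on all available post-baseline data from all randomised patients, with arm, visit, arm-by-visit and baseline score as fixed effects. Report the adjusted arm difference with its 95% confidence interval.
- **Single-time comparisons.** Use ANCOVA with the baseline score in place of the t test, or name the baseline score as a covariate in the regression already planned.

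State that the mixed model assumes data missing at random, and say separately how deaths enter the comparison, since the model does not settle that.

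Cost: a change of wording and slightly more analysis work. The software stays the same and no extra patients are needed.

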## Discussion

The general purpose of this protocol is to assess the efficacy of a mobile app in the follow-up of patients under home oxygen therapy through an intervention aimed at decreasing acute exacerbations. Moreover, this protocol intends to determine the suitability of oxygen system prescriptions and to identify oxygen supply underuse at home. This intervention will be assessed through a randomized, two-arm clinical follow-up. Literature suggests that the use of mobile devices to monitor patients’ health or locate patients with chronic diseases or conditions has become possible [36, 37]. Mobile apps can provide public healthcare, improve community data collection, or provide remote assistance for controlling medical data of patients with chronic diseases [38, 39]. Certain studies show that the use of mobile devices can improve decision-making processes and diagnostic suitability and provide immediate access to multiple medical data sources [40–42]. If the results of our clinical trial suggest a positive effect, we will demonstrate that the continuous monitoring of patients on home oxygen therapy, and the creation of a direct link with their caregivers, will result in a decrease in complications and an optimization of home oxygen management.

## Data Availability

not Applicable. As the submitted article is a clinical trial protocol, the authors do not have a database to share it in any public repository. Once the clinical trial is completed, the investigators will decide the most appropriate way to make them public.

## Abbreviations

CHOT: Continuous home oxygen therapy
APP: Applications
ICT: Information and communication technologies
E-HEALTH: Information and communication technologies set
DT: Duration time of the oxygen cylinder
FL: Flow
F: Conversion factor
P: Pressure of the cylinder
RP: Residual pressure
SatO_2_: Saturation of oxygen
FiO_2_: Fraction of inspired oxygen
